## Abstract

**Background:**

Up to 65% of people with multiple sclerosis (PwMS) develop cognitive deficits, which hampers their ability to work, participating in day-to-day life and ultimately reducing quality of life (QoL). Early cognitive symptoms are often less tangible to PwMS and their direct environment and are noticed only when symptoms and work functioning problems become more advanced, i.e., when (brain) damage is already advanced. Treatment of symptoms at a late stage can lead to cognitive impairment and unemployment, highlighting the need for preventative interventions in PwMS.

**Aims:**

This study aims to evaluate the (cost-) effectiveness of two innovative preventative interventions, aimed at postponing cognitive decline and work functioning problems, compared to enhanced usual care in improving health-related QoL (HRQoL).

**Methods:**

Randomised controlled trial including 270 PwMS with mild cognitive impairment, who have paid employment ≥ 12 h per week and are able to participate in physical exercise (Expanded Disability Status Scale < 6.0). Participants are randomised across three study arms: 1) ‘strengthening the brain’ – a lifestyle intervention combining personal fitness, mental coaching, dietary advice, and cognitive training; 2) ‘strengthening the mind’ – a work-focused intervention combining the capability approach and the participatory approach in one-on-one coaching by trained work coaches who have MS themselves; 3) Control group—receiving general information about cognitive impairment in MS and receiving care as usual. Intervention duration is four months, with short-term and long-term follow-up measurements at 10 and 16 months, respectively. The primary outcome measure of the Don’t be late! intervention study will be HRQoL as measured with the 36-item Short Form. Secondary outcomes include cognition, work related outcomes, physical functioning, structural and functional brain changes, psychological functioning, and societal costs. Semi-structured interviews and focus groups with stakeholders will be organised to qualitatively reflect on the process and outcome of the interventions.

**Discussion:**

This study seeks to prevent (further) cognitive decline and job loss due to MS by introducing tailor-made interventions at an early stage of cognitive symptoms, thereby maintaining or improving HRQoL. Qualitative analyses will be performed to allow successful implementation into clinical practice.

**Trial registration:**

Retrospectively registered at ClinicalTrials.gov with reference number NCT06068582 on 10 October 2023.

## Background

Multiple sclerosis (MS) is a chronic, neurodegenerative, and demyelinating disease of the central nervous system [1]. Globally, the disease counts around 2.5 million cases. MS is usually diagnosed when people are between 20 and 40 years old, making it the most prevalent cause of disability in young adults of working age [2, 3]. MS causes a wide variety of symptoms, with fatigue, cognitive, and motor problems commonly reported [4]. Up to 65% of people with MS (PwMS) develop cognitive deficits [5, 6], which severely affect daily life functioning and ultimately health-related quality of life (HRQoL) [7]. About 65% of all PwMS become unemployed within 5 years after diagnosis [8–10], with cognitive impairment being one of the main reasons for unemployment and work-related problems [11, 12].

### MS and cognitive rehabilitation

Current rehabilitation for cognitive impairment in PwMS is limited and focusses mostly on restorative and compensatory strategies [13]. Previous studies consistently demonstrate mild-to-moderate effects of cognitive training on cognitive performance in PwMS (i.e., functional training [14]). A recent study suggests that people with relapsing remitting MS (RRMS) and larger grey matter volume were more likely to improve on information processing speed after cognitive training compared to people with progressive MS (PMS) and grey matter atrophy [15]. Furthermore, another study provides similar results in that there might be an early window of opportunity for cognitive training as PwMS with an intact brain network (compared to healthy controls) benefited from a cognitive rehabilitation programme, while PwMS with brain network deficits did not show beneficial effects from the intervention [16]. Next to cognitive training, earlier work has also shown that physical exercise appears to improve cognitive functioning in PwMS [17, 18]. Studies have shown that both cognitive training and exercise positively influence brain functioning [19–22]. Enhanced effects can be expected from the combination of cognitive training and exercise, as was illustrated in patients with mild cognitive impairment and Alzheimer’s disease [23]. However, the actual effects of such a combination on cognition still need to be established in PwMS.

### MS and work

With respect to work-related problems, interventions are typically only provided when PwMS are already on sick leave or have lost their job [24]. These interventions might therefore be too late, as having and keeping a job is important for people’s social contacts, self-respect and to feel valued [25]. In addition, job and/or productivity loss have economic consequences for both the PwMS as well as society at large [26]. For instance, already for the mildly affected MS group (expanded disability status scale score (EDSS) 0–3), the mean utility (i.e., value for given states of health between 1 (full health) and 0 (death)) and annual MS-related healthcare costs were estimated at 0.744 and €23,100 in the Netherlands respectively, which primarily resulted from productivity losses [27]. Research on work-related interventions for PwMS is directly needed but remains scarce. In fact, in recent years the ability to work and being employed increasingly received attention within healthcare research. This is not surprising as work participation is a significant determinant of HRQoL in PwMS, independent of their experienced health [28]. The Dutch government encourage individuals with a chronic disease such as MS to self-manage and take control of their lives, including their work [29]. However, self-managing daily demands in a dynamic work context where activities request a high level of cognitive and psychological skills is challenging. For PwMS, being able to work is therefore not only a matter of self-management of work challenges but is also highly dependent on the work context. A supportive work environment that is willing to adjust and fine-tune the work to the cognitive abilities of the employee and to provide emotional support is imperative for workers with chronic diseases such as MS to be able to remain employed [30]. As such, a proactive and timely work-related intervention that includes active involvement of the workplace may enable patients to effectively deal with work challenges and prevent sick leave and job loss.

### Don’t be late!

While the physical limitations of MS can (partly) be compensated with mobility aids (e.g., wheelchair, orthoses) and workplace adjustments, such solutions are scarce for cognitive deficits. Currently, interventions for cognitive impairments and work-related problems start when these problems are often already too advanced and difficult to overcome [25]. This triggers a negative cascade of events that inevitably leads to further cognitive deterioration, unemployment and decreased HRQoL. Therefore, it is of great importance to intervene in the early stage of cognitive impairment.

The Don’t be Late! project aims to provide timely intervention in PwMS with mild cognitive impairment who are still employed. The primary aim is to investigate the effectiveness of two innovative interventions as compared to enhanced usual care in improving HRQoL. These interventions are aimed at preventing and/or postponing cognitive decline and work-related problems. Secondary aims are, 1) to assess the effectiveness of the investigated interventions in improving cognitive, psychological and work functioning, and in enhancing the brain’s functional network, 2) to examine which factors (i.e., baseline cognitive, psychological, work and brain MRI-parameters) are predictive of the response to the investigated interventions, 3) to assess which mechanisms mediate the effect of the investigated interventions on HRQoL, and 4) to assess the cost-effectiveness of the investigated interventions.

For the qualitative study, the primary aim is to qualitatively reflect on the process and outcome of the investigated interventions considering the perspectives of relevant stakeholders and to investigate how to foster smooth and successful implementation in clinical practice.

## Methods/design

### Study design and setting

The Don’t be late! research project consists of three work packages, of which this protocol describes the second and third.

Work package 1—‘Timely identification of cognitive decline in Multiple Sclerosis’ aims to 1) identify early cognitive decline in PwMS, and 2) to validate the Multiple Screener in 750 PwMS, a digital tool for administering neuropsychological tests in PwMS [31].

Work package 2 concerns a randomised controlled trial containing two intervention arms (‘strengthening the brain’ and ‘strengthening the mind’) and a control condition (‘enhanced usual care’). This study follows a repeated-measures design and is performed at Amsterdam UMC and Leiden University, the Netherlands. Participants will be selected from a pool of eligible participants from work package 1 and participants will be recruited through other studies in which they indicated that they could be approached for further research participation, as well as through social media channels. Eligible individuals will be randomised over the three arms. Results of measurements for work package 2 overlapping with work package 1 will be adapted from work package 1 for participants included through work package 1.

Work package 3 is a qualitative study using semi-structured interviews with representatives from all stakeholder groups to investigate the process of the interventions. Additionally, focus groups are used to provide a deeper understanding of the results of the interventions and to investigate how to successfully implement the interventions into clinical practice.

### Study population

#### Work package 2: Randomized controlled trial

We aim to include 270 participants in the randomized controlled trial. In order to be eligible to participate, PwMS must meet the following criteria: (1) confirmed MS diagnosis according to the McDonald 2017 criteria [32], (2) age between 18 and 67, (3) no changes in disease modifying therapy in the last three months prior to inclusion—this criterion only applies at inclusion to ensure participants are in a stable situation at the start of the study and for follow-up measures, changes in treatment will be registered but will not result in exclusion from the study, (4) no current relapse or steroid treatment in the six weeks prior to study visits, (5) presence of mild cognitive deficits (at least one test with a Z-score of -1.0 to -1.99 below norm scores of healthy controls on the Minimal Assessment of Cognitive Function in Multiple Sclerosis (MACFIMS) battery [33]; not fulfilling the criteria for severe cognitive impairment (Z-score of -2.0 on ≥ 2 tests)), (6) performing paid work for at least 12 h per week, (7) being able to participate in an exercise intervention (i.e., EDSS < 6.0), and (8) fulfilling safety criteria for MRI (no metal inside body, not pregnant, no claustrophobia). Exclusion criteria are (1) presence of neurological (other than MS) and psychiatric disorders, (2) a current or history of drug or alcohol abuse, (3) being unable to speak or read Dutch, (4) currently on sick leave for a period of 6 weeks or longer, and (5) currently pregnant.

### Interventions

Participants will be randomly allocated into one of three groups, ‘*strengthening the brain’*, ‘*strengthening the mind’*, or ‘*enhanced usual care’*. The interventions ‘strengthening the brain’ and ‘strengthening the mind’ have a duration of four months and will be optimised towards a participant’s personal needs. The enhanced usual care group is acting as control group where participants are asked to continue life ‘as is’ for the duration of the intervention (4 months).

#### Strengthening the brain

‘Strengthening the brain’ is a lifestyle intervention which combines physical exercise with cognitive training.

For the exercise component, participants receive exercise and lifestyle coaching (part in kind contribution of Personal Fitness Nederland, Fit for Life programme, www.personalfitnessnederland.nl) where one-on-one training will be provided at one of the 94 studios of Personal Fitness Nederland (PFN). Every session will exist of a combination of cardio (aerobic) and strength (anaerobic) training dependent on the goals of the participant. At the start of the programme an intake will take place, where the physical fitness of the participant will be determined, and attention will be paid to specific health issues and goals of the participant. Sessions will be made increasingly more challenging. Each session will start with weighing the participant followed by 30 min of exercise in a studio where no other people are present, guaranteeing full attention to the participant. Next to the weekly face-to-face sessions, participants are asked to perform pre-set exercises at home twice a week (20 min each) which are guided by instruction videos on an online platform. A quantitative assessment of the adherence (how many sessions attended and progress between training sessions) will be done by the lifestyle coach and participants will write down their goals concerning exercise and diet for the upcoming week in a personal log. Lifestyle coaches will also provide participants with diet schemes and mental coaching. This will also be recorded using the personal log.

For the cognitive component, participants will follow cognitive training using a Dutch home-based computerised cognitive training, BrainGymmer^©^ (https://www.Braingymmer.com), which has been used in multiple studies [34–37]. A variety of cognitive functions are trained (information processing speed, spatial memory, working memory, executive functioning) rather than one cognitive function in particular. The cognitive training will focus on the cognitive function that was most impaired on the neuropsychological assessment at baseline. The training has an adaptive mechanism, which will adjust to the participant’s performance level to make it challenging for all participants. The programme will log training time and the percentage of correctly performed games. Participants are instructed to train for 60 min per week.

#### Strengthening the mind

The ‘strengthening the mind’ intervention consists of biweekly contact with trained work coaches who are all diagnosed with MS themselves (in kind contribution of the Dutch MS Society, MSVN). The intervention focuses on (re)discovery of a sustainable and healthy balance between relevant work values, the challenges workers with MS are facing, and at the same time meeting the work demands in a dynamic work context with ongoing technological developments. This will be reached using a combination of the capability approach and the participatory approach: “Working Positively”. The starting point of the capability approach related to work participation is to explore what people find important and valuable in work – what they would like to achieve in a given (work) context – and moreover, in the case of individuals confronted with a chronic and progressive disease such as MS, to ascertain whether people are enabled and able to do so. The participatory approach uses a practical, stepwise manner to detect challenges at the workplace and implement solutions by actively involving both the worker and the workplace (e.g., the supervisor).

Every participant will be matched with a trained work coach that also has an MS diagnosis. The starting point (step 1) of the coaching will be an assessment of individual work values using the capability set for work questionnaire [38] and to become acquainted with the worker and their working context. This starts by identifying which work values are important to the worker with MS. Secondly, it will be assessed to what extent workers are enabled to achieve these values at work, and thirdly to what extent they are able to achieve these values at work. Any discrepancies patients experience in being enabled and able to achieve important work values will be flagged, as these indicate barriers for optimal and satisfactory work participation [39]. Additionally, the employer or other representative of the workplace will be requested to join at least one coaching session to provide information related to work demands and context from their perspective as is described as an essential element of the participatory approach. In case the participant prefers not to disclose their MS diagnosis to the workplace, an independent occupational health professional may act as a representative of the workplace.

In the second step of this intervention, both the worker and the representative of the workplace prioritise the important values and challenges to meet work demands (e.g., work tasks, time pressure, working hours, peak loads, or other challenges within the working context). The worker and representative of the workplace will select three work challenges that will be addressed during the coaching period. Third, for each work challenge both the worker and the representative of the workplace will think of possible and practical solutions under guidance of the coach. Fourth, a plan of action is developed in which consensus for the proposed solutions are achieved and a plan for its execution is agreed upon. The fifth step describes and ensures the implementation of solutions, and in the final step the degree and the effects of the implemented solutions will be evaluated with all stakeholders involved. If necessary, the plan of action is adjusted [40]. The intervention is completed either when satisfactory solutions have been implemented for all identified work challenges, or after biweekly coaching has taken place for a period of 4 months.

#### Enhanced usual care

Participants in the enhanced usual care condition will watch a pre-recorded video together with a researcher with the opportunity to ask questions afterwards. The video provides a standardised explanation of cognitive decline in PwMS based on the Dutch book “MS and Cognition, by scientists for people with MS and their surroundings” (editors: [name] & [name]). The video includes information about the frequently affected cognitive domains in MS and their relation to brain pathology. Participants will be asked to continue their life ‘as is’ during the time of the intervention (4 months). The main reason for incorporating enhanced usual care in the protocol is to avoid resentful demoralisation of participants assigned to this group.

### Outcome measures

#### Work package 2: Randomized controlled trial

As illustrated in Figs. 1 and 2, measurements in the randomized controlled trial will take place right before the intervention (baseline; T0), directly after the intervention (four months after baseline; T1), at short- and long-term follow-up (10 months (T2) and 16 months (T3), respectively).

**Fig. 1 Fig1:**
[figure not shown]
Participant timeline of Don’t be late! project. WP = work package

**Fig. 2 Fig2:**
[figure not shown]
Time points of all assessments. t0 = baseline, t1 = month 4, directly after intervention, t2 = month 10, short-term follow-up, t3 = month 16, long-term follow-up

#### Demographic and disease-related measures

During the baseline assessment, demographic and clinical characteristics will be gathered from the participants. The following characteristics will be determined: Age, sex, length, weight, highest level of education attained, job type, working hours, disability pension, current and history of exercise activity, year of diagnosis, MS subtype, disease duration, disease severity using EDSS, and medication history.

#### Primary outcome measure

The primary outcome measure of this study is HRQoL, which will be assessed using a composite score of the 36-item Short Form (SF-36) [41]. HRQoL will be determined at all four measurement moments during the study, which will allow to assess short-term and long-term changes in HRQoL. The effects of the interventions on the SF-36 as overall value and per subcategory will be analysed for timepoints T1, T2, and T3. Subcategories of the SF-36 contain physical functioning, role limitations because of physical health problems, bodily pain, social functioning, general mental health, role limitations because of emotional problems, vitality, and general health perceptions. The validity and reliability of the SF-36 are well established in healthy controls and PwMS [41, 42].

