### Sample size

The sample size of 270 participants is based on a power calculation. A review of earlier studies on the effects of cognitive rehabilitation in MS [14] suggests that we can expect moderate effects (effect size of 0.35) between pre- and post-intervention. Assuming statistical significance of 0.025, a power of 0.80, and an effect size of 0.35, 75 participants per group are needed. A conservative alpha of 0.025 has been chosen to take into account that we compare two interventions with a control group. A correlation of 0.6 between the measures was assumed. Based on previous experiences, a drop-out of 20% over the study period is expected. Therefore, we will include 90 subjects per group to ensure sufficient power. This study will be carried out using an intention-to-treat protocol. Therefore, subjects who withdraw from the study after inclusion will not be replaced.

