### Statistical analysis

Data will be analysed using R (R Core Team, Vienna, Austria) and Rstudio version 4.2 or higher (PBC, Boston, MA) and/or SPSS version 28 or higher (IBM, Armonk, NY). Analyses will be performed according to intention-to-treat and per-protocol. The main focus of the analyses will be on the intention-to-treat analysis, as this will reduce bias and better represents daily practice. A per-protocol analysis will be performed to evaluate the effect of the intervention on itself, supplementary to the intention-to-treat analysis. Data will be included in the per-protocol analysis if the participant completed the intervention. The alpha level will be set at a statistical threshold of α = 0.05, corrected for multiple comparisons when applicable. GAS will be used to discriminate between responders and non-responders concerning the interventions.

For the outcome cognitive functioning we will calculate a reliable change index (RCI) for each cognitive test based on the enhanced usual care group. Using the RCI scores allows us to correct for learning effects. An RCI score above + 1.64 or below -1.64 is assumed to reflect significant improvement or decline, respectively [5, 103]. The psychological and work functioning data will be obtained via questionnaires and will be analysed as continuous variables together with the physiological data. MRI images will be analysed using FSL (https://fsl.fmrib.ox.ac.uk) and Freesurfer (Charlestown, Massachusetts). Data obtained (atrophy, white matter integrity, task-specific brain activation and brain connectivity) will be exported to Rstudio after which mixed-model analyses will be performed.

Missing data will be minimised by using digital questionnaires, that prompt participants to answer each question before being allowed to proceed. For other outcome measures, multiple imputation will be used for missing baseline and follow-up data. Outliers will be identified and excluded from the main analysis.

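### No primary timepoint or summary contrast is fixed for the SF-36 overall score, and the stated alpha allowance covers two interventions but not three visits

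*Protocol article*

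**What the plan says.** Four places in the protocol article bear on this.

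- **Primary outcome measure.** The outcome is an SF-36 composite, measured at all four assessments. The analysis is described as "The effects of the interventions on the SF-36 as overall value and per subcategory will be analysed for timepoints T1, T2, and T3". No visit is ranked above another.
- **Statistical analysis, primary analyses.** Each intervention is compared with enhanced usual care on the overall SF-36 score. The model has time (four levels, including baseline) and condition (three levels) as fixed factors and subject as a random factor. No time-by-condition term, decisive visit or average over visits is named.
- **Sample size.** "A conservative alpha of 0.025 has been chosen to take into account that we compare two interventions with a control group". The calculation is "Assuming statistical significance of 0.025, a power of 0.80, and an effect size of 0.35, 75 participants per group are needed", and the effect comes from a review that "suggests that we can expect moderate effects (effect size of 0.35) between pre- and post-intervention".
- **Statistical analysis, general.** "The alpha level will be set at a statistical threshold of α = 0.05, corrected for multiple comparisons when applicable". Neither the family of tests nor the method of correction is given.

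**The concern.** The scale and the arm comparisons are fixed, but the time dimension of the primary claim is not. Two interventions at three visits give six candidate results on the overall score, and the stated reason for the 0.025 accounts only for the factor of two.

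The text also points in different directions. The pre- to post-intervention effect used for sizing suggests T1, at month 4. The Discussion presents the long follow-up as a strength, which suggests T3, at month 16. A benefit seen only at month 4 and one seen only at month 16 could each be reported as a positive primary result.

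The listed model does not settle this. With time and condition as main effects only, the condition effect is averaged over all four assessments, including T0, before any treatment. At stake are the false-positive rate of the main claim and, if the gap is closed by correcting over all six tests, the power.

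**Working it through.** **Inputs**
- From the article: two interventions sharing one control, 1:1:1 allocation (Allocation and blinding); three post-baseline visits; alpha 0.025 and power 0.80; "A correlation of 0.6 between the measures was assumed".
- Assumed: two-sided tests (the article does not say), normal test statistics, the 0.6 applying to every pair of visits, and no true effect in either arm when error rates are computed.

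**Step 1. The plan's own allowance.** 0.05/2 = 0.025 for each intervention. With equal arms and a shared control, the two test statistics correlate at 0.5. For one contrast per intervention at two-sided 0.025 (critical value 2.241), the bivariate normal distribution gives

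P(at least one false positive) = 1 − P(|Z1| < 2.241 and |Z2| < 2.241) = 0.0465.

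If the two tests were independent, it would be 1 − 0.975² = 0.0494. The allowance does its job when one contrast per intervention is decisive.

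**Step 2. Any of three visits counts, each test at 0.025.** There are 2 × 3 = 6 tests. The correlation between visits within one intervention depends on the estimator:
- visit means: 0.6
- change from baseline: 0.5
- baseline-adjusted: (0.6 − 0.6²)/(1 − 0.6²) = 0.24/0.64 = 0.375

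The six-dimensional normal distribution, with correlation 0.5 between interventions combined with these values, was simulated with 400,000 draws per row. A repeat with 2,000,000 draws agreed to within about 0.001.

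| Estimator | Each test at 0.025 | Each test at 0.05/6 = 0.00833 |
|---|---|---|
| Visit means | 0.111 | 0.040 |
| Change from baseline | 0.119 | 0.043 |
| Baseline-adjusted | 0.125 | 0.045 |

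The bound for six independent tests at 0.025 is 1 − 0.975⁶ = 0.141.

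**Step 3. Correct over all six instead.** Bonferroni at 0.00833 keeps the family-wise error at 4.0 to 4.5%. A test with exactly 80% power at two-sided 0.025 has expected statistic 2.241 + 0.842 = 3.083. The critical value at 0.00833 is 2.638, so its power becomes Φ(3.083 − 2.638) = Φ(0.445) ≈ 0.67. Keeping 80% would multiply the sample size by ((2.638 + 0.842)/(2.241 + 0.842))² = (3.480/3.083)² ≈ 1.27.

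Step 3 takes the planned 80% at face value. The stated 75 per group was not reproduced from the stated inputs: standard two-group formulas at two-sided 0.025 gave 156 with no use of the correlation, 125 for change scores, 100 for a baseline-adjusted single visit and 58 for a baseline-adjusted average of three visits. That is a separate matter and nothing here depends on it. The spread does show that the choice of contrast governs the power as well as the error rate.

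**The case against.** **The alphas.** A reader might infer that 0.025 in one section and 0.05 in another conflict. They do not. 0.025 is 0.05/2, and the analysis section says that the 0.05 is corrected for multiple comparisons. The natural reading is an overall level and a per-comparison level.

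**The subcategories.** A reader might count the overall score plus eight subcategories at three visits for two interventions, 9 × 3 × 2 = 54 tests, and arrive at error rates above 50%. The primary-analysis paragraph limits the primary test to the overall score, and nowhere does the article say that a significant subcategory would be a positive primary result. Such figures also need a correlation between subcategories that the article does not give.

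**No correction at all.** Testing all six at 0.05 would give about 21 to 23%. That assumes no correction is made, against what both sections say.

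**One model, and a plan not shown.** The primary analysis is a single mixed model, from which visit-specific estimates may simply be reported. This is a condensed article, and the exact correction method may properly sit in a statistical analysis plan. An interaction term may also be intended though not listed.

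The first three objections stand in full. The fourth stands in part: the missing correction method is not held against the article. The article does, however, state the three-visit analysis and state what its allowance is for, and the second does not cover the first. Which visit or summary decides the trial defines its main claim, so this is more than omitted detail.

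**Conclusion.** The point holds in a limited form. The scale and the between-arm comparisons are named. The decisive visit or summary over time is not, and the 0.025 allowance accounts for two interventions only.

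The size is conditional. The family-wise error is about 4.7% if one contrast per intervention is decisive. It is about 11 to 12.5% if a win at any visit counts at 0.025 each. If all six tests are Bonferroni-corrected, the error is controlled but power per test falls from a nominal 80% to about 67%. These figures rest on two-sided tests, a common correlation of 0.6 and normal statistics. The article does not say that a win at any visit would count, so an inflated error rate is a risk left open by the text, not an established property of the plan.

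**What to change.** 1. In the primary-analyses paragraph, name one confirmatory contrast per intervention against enhanced usual care on the SF-36 overall score. It may be the difference at one named visit, or the baseline-adjusted average over T1 to T3, taken from a model that includes a time-by-condition term. Test each at two-sided 0.025.
2. Where the 0.05 level is set, state that this split is how it is corrected for the primary outcome, in place of the open-ended qualifier.
3. Under Primary outcome measure, label the remaining visits and the eight subcategories secondary, reported as estimates with confidence intervals.
4. Make the Sample size section refer to the same contrast.

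A fixed testing order over visits, or a stated correction over the six tests, would also control the error; the latter costs power as shown above. The cost of the recommended change is wording, plus the loss of confirmatory status for the other visits. The article reports recruitment as ongoing, so the choice should be made and dated before any outcome data by arm are seen.
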